## 4.0 SELECTION AND ENROLLMENT OF SUBJECTS

### 4.1 Inclusion Criteria

4.1.1 HIV-1 infection acquired in the previous 12 months, as defined by one of the following:

- *Positive HIV plasma viral load and negative HIV antibody test*
- *Positive HIV plasma viral load and indeterminate HIV antibody test*
- *Positive HIV plasma viral load and positive HIV antibody test WITH:*
  - *Negative detuned HIV antibody test*
  - *OR documented negative HIV antibody test within the past 12 months*

4.1.2 No prior antiretroviral therapy (other than post-exposure prophylaxis)

4.1.3 For subjects who have been infected with HIV-1 for more than six months at study entry: HIV-1 RNA > 5,000 copies/mL obtained within 30 days of initiation of therapy performed by any laboratory that has a CLIA certification or its equivalent.

4.1.4 Laboratory values obtained within 30 days of initiation of therapy:

- Absolute neutrophil count (ANC) ≥ 750/mm^3^.
- Hemoglobin ≥ 7.0 g/dL.
- Platelet count ≥ 50,000/mm^3^.
- Creatinine ≤ 3 x upper limit of normal (ULN).
- AST (SGOT), ALT (SGPT), and alkaline phosphatase ≤ 5 × ULN.
- Total bilirubin ≤ 2.5 x ULN.

4.1.6 Negative serum pregnancy test at screening and negative urine or serum pregnancy test at the time of initiation of therapy in women of childbearing potential.

4.1.7 Age ≥ 18 years*.*

4.1.8 Ability and willingness of subject to give written informed consent.

- - 1. Ability to swallow tablets/capsules.
    2. Willingness to use barrier methods of contraception.

### 4.2 Exclusion Criteria

4.2.1 Inability to design a HAART regimen based on the results of genotypic resistance testing.

4.2.2 Two CD4+ cell count measurements <350 cells/mm^3^ obtained at least 7 days apart within 30 days of initiation of therapy obtained at laboratories that have a CLIA certification or its equivalent**.**

4.2.3 For subjects who have been infected with HIV-1 for more than six months at study entry:HIV-1 RNA < 5,000 copies/mL obtained within 30 days of initiation of therapy, measured in a laboratory that has a CLIA certification or its equivalent.

4.2.4 Pregnancy or breast-feeding.

4.2.5 Use of systemic cancer chemotherapy, systemic investigational agents, specific antiretroviral medications (with the exception of antiretroviral agents given for post-exposure prophylaxis), immunomodulators (growth factors, systemic corticosteroids, HIV vaccines, immune globulin, interleukins, interferons) within the past 30 days.

4.2.6 Active drug or alcohol use or dependence that, in the opinion of the investigator, would interfere with adherence to study requirements.

4.2.7 Serious illness requiring systemic treatment and/or hospitalization until subject either completes therapy or is clinically stable on therapy, in the opinion of the investigator, for at least 7 days prior to study entry.

4.2.8 Inability to sign informed consent.

### 4.3 Study Enrollment Procedures

4.3.1 Prior to implementation of this protocol, sites must have the protocol and consent form approved by their local institutional review board (IRB). Sites must be registered with and approved by the DAIDS Regulatory Compliance Center Protocol Registration Office.

Once a candidate for study entry has been identified, details will be carefully discussed with the subject. The subject will be asked to read and sign the consent form that was approved by the local IRB and the DAIDS Regulatory Compliance Center Protocol Registration Office.

4.3.2 The Division of AIDS has concluded that this protocol does NOT meet Federal requirements governing prisoner participation in clinical trials and should NOT be considered by local IRBs for the recruitment of prisoners. Participants who become incarcerated during the course of their participation in the study, will not be dis-enrolled, and will resume study participation at the time of their release.

4.3.3 Once it has been established that all inclusion and exclusion criteria have been met, study subjects will be randomized to receive TL-HAART or not through an automated randomization process at the Canadian HIV Trials Network, as detailed in the case report forms.

**4.4 Co-Enrollment Guidelines**

All subjects should be encouraged to enroll in the AIEDRP CORE01 Database Protocol.

## 5.0 STUDY TREATMENT (OR INTERVENTION)

5.1 Regimens, Administration, and Duration

All antiretroviral drugs to be used within this protocol will be licensed for sale for the treatment of HIV infection in Canada and the United States at the time and place at which they are used. (Table A) They will be prescribed and administered according to the version of the DHHS guidelines that are current at the time treatment is given. In Canada, all medications are 100% reimbursed by provincial drug plans. We will use once daily dosing and directly observed therapy (DOT) when appropriate. In Baltimore, most of the medications will be donated by pharmaceutical companies, or will be available free of charge from the MADAP program of the state of Maryland, or will be paid for by patient’s insurance. Study funds will be available to cover co-payments for drugs purchased through patient’s insurance. Combinations of two nucleoside/nucleotide analogues and a third or fourth agent will be used in all cases. (Note: ritonavir used for the purpose of boosting another protease inhibitor will not be considered an additional agent) As new drugs become licensed, they will be available to be used in this protocol. All patients who are randomized to receive HAART will have treatment discontinued after twelve months of therapy unless there is a medical contraindication to doing so, such as chronic HBV infection, CD4 cell count < 350 cells/mm^3^, or pregnancy. Patients who are receiving a non-nucleoside reverse transcriptase inhibitor will substitute a protease inhibitor (with or without ritonavir boosting) for 2-4 weeks prior to discontinuation of the entire regimen, if this is judged to be appropriate by the study physician.

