### 1.2 Primary Objective

To compare the steady state viral load (plasma HIV RNA concentration) in patients who have received TL-HAART to that achieved in similar patients who did not receive any antiretroviral treatment.

###

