A Western blot will be considered negative if no bands are present, and indeterminate if some bands are present but criteria for positivity are not met. If more than one set of circumstances is met, the first will be applied.

Staging of HIV infection (acute vs. early) will be determined using the AIEDRP algorithm (Appendix V)

Taken as a whole, our approach will allow for a precise classification of individuals according to the timing of infection, enhancing our ability to test the protocol’s main hypothesis in the overall study group as well as in sub-groups representing earlier infection.

Those who agree to take part in the clinical trial and meet the inclusion criteria will be randomized either to receive TL-HAART, or to be followed off therapy. After eligibility has been established, patients will be seen within 14 days (of screening) for randomization, then at weeks 1, 2, and 4 (1 month), then every month for the next 11 months over the one-year randomization period. Thereafter, follow-up will be quarterly for the duration of the study.

For those randomized to receive therapy, the specific regimen will be selected by the study physician and the participant, according to DHHS guidelines current at the time of initiation of HAART, and modified as necessary based on the results of genotypic resistance testing conducted in real time. Early on, the evolution of anti-HIV antibodies will be measured if a fully positive Western blot test was not present at baseline. On a number of occasions, more extensive blood sampling will be done, for storage of serum, plasma, and peripheral blood mononuclear cells to test additional virologic and immunologic hypotheses that will be generated in the course of this work.

In treated patients, TL- HAART will be discontinued after 12 months of therapy, unless there is a medical contraindication to doing so, such as chronic HBV infection, CD4 cell count

< 350, or pregnancy.

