6.1.1 Prestudy evaluations

Screening

Screening evaluations to determine eligibility must be completed no more than 14 days before study randomization.

Entry

Entry evaluations must occur within 14 days of the completion of all screening evaluations. In the event that results of the genotype are not available, the patient will be randomized and if necessary his/her HAART regimen will be adjusted upon receipt of the genotype. Subjects are expected to start treatment within 24 hours of randomization. (section 6.2.3).

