APPENDIX II

SCHEDULE OF EVALUATIONS

|  | **Screening** | **Entry** | **Weeks** |  | **Months^(7)^** | |  |  |  |  |  |  |  |  |  |  |  |
| --- | --- | --- | --- | --- | --- | --- | --- | --- | --- | --- | --- | --- | --- | --- | --- | --- | --- |
| **Test** |  | Day 0 | 1 | 2 | 1 | 2 | 3 | 4 | 5 | 6 | 7 | 8 | 9 | 10 | 11 | 12^(4)^ | 15^(3)^ |
| **Medical History** | X |  | X* | X* | X* | X* | X* | X* | X* | X^*^ | X* | X* | X* | X* | X* | X* | X* |
| **Medication History** | X |  | X | X | X | X | X | X | X | X | X | X | X | X | X | X | X |
| **Randomization** |  | X |  |  |  |  |  |  |  |  |  |  |  |  |  |  |  |
| **Risk Behavior** | X |  | X | X | X | X | X | X | X | X | X | X | X | X | X | X | X |
| **Physical Exam** |  | X | X* | X* | X* | X* | X* | X* | X* | X* | X* | X* | X* | X* | X* | X | X* |
| **Adherence Questionnaire** |  |  | X | X | X | X | X | X | X | X | X | X | X | X | X | X | X |
| **CBC**** | 3 | 3 | 3 | 3 | 3 | 3 | 3 | 3 | 3 | 3 | 3 | 3 | 3 | 3 | 3 | 3 | 3 |
| **Chemistry Panel**** | 10 | 10 | 10 | 10 | 10 | 10 | 10 | 10 | 10 | 10 | 10 | 10 | 10 | 10 | 10 | 10 | 10 |
| **Lipid panel**** | 5 |  |  |  |  |  |  |  |  |  |  |  |  |  |  | 5 |  |
| **CD4+ cell count**** | 5 |  |  |  |  |  | 5 |  |  | 5 |  |  | 5 |  |  | 5 | 5^(6)^ |
| **Viral Load**** | 5 | 5 |  |  | 5 | 5 | 5 | 5 | 5 | 5 | 5 | 5 | 5 | 5 | 5 | 5 | 5^(6)^ |
| **HIV EIA/WB (2)** | X | X^(1)^ | X^(1)^ | X^(1)^ | X^(1)^ | X^(1)^ |  |  |  |  |  |  |  |  |  |  |  |
| **Repository**** | 50 |  |  |  | 50 | 10 | 50 | 50 | 10 | 50 | 10 | 50 | 10 | 50 | 10 | 50 | 50 |
| **Hepatitis B S AB^**^** | 2 |  |  |  |  |  |  |  |  |  |  |  |  |  |  |  |  |
| **Hepatitis B S Ag^**^** | 3 |  |  |  |  |  |  |  |  |  |  |  |  |  |  |  |  |
| **Hepatitis C ab^**^** | 2 |  |  |  |  |  |  |  |  |  |  |  |  |  |  |  |  |
| **Genotype**** | 5^(2)^ |  |  |  |  |  |  |  |  |  |  |  |  |  |  |  | 5^(2)^ |
| **TOTALS** | 83 | 18 | 13 | 13 | 68 | 23 | 73 | 68 | 28 | 73 | 23 | 63 | 23 | 63 | 23 | 78 | 73 |

* Vital Signs and Symptoms; interim medical history, symptom driven PE when necessary

**The numbers in the individual boxes indicate the amount of blood (in mL) that will be collected for the indicated test or procedure.

(1) If initially negative or indeterminate, will be repeated until fully positive

(2) Will be done on all patients at baseline, on anyone who experiences virologic failure while on treatment (as defined in section 5.2), and at month 15 on pts who discontinued HAART at month 12.

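### Patients who are HBsAg-positive at screening are randomised and enter the off-treatment set-point comparison, although chronic HBV is a named reason not to stop HAART

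*Protocol*

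**What the plan says.** - **Stopping at month 12.** Section 5.1 has HAART stopped after twelve months "unless there is a medical contraindication to doing so, such as chronic HBV infection"; it also names a CD4 count below 350 and pregnancy. Section 3.0 carries the same exception.
- **Testing.** Appendix II lists "Hepatitis B S Ag" in the screening column only. Section 6.1.1 places screening before allocation: "Screening evaluations to determine eligibility must be completed no more than 14 days before study randomization".
- **Eligibility.** Section 4.3.3 reads "Once it has been established that all inclusion and exclusion criteria have been met, study subjects will be randomized to receive TL-HAART or not". Neither 4.1 nor 4.2 has a hepatitis B item. The other two named reasons for not stopping do appear at entry in some form: 4.2.2 (two CD4 counts below 350 at least 7 days apart) and "4.2.4 Pregnancy or breast-feeding".
- **What is to be estimated.** Section 1.2: "To compare the steady state viral load (plasma HIV RNA concentration) in patients who have received TL-HAART", against similar patients given no antiretroviral treatment. Section 9.4 places the set-point readings 12 and 24 months after the randomised year, and section 6.1.6 describes treated-arm follow-up after that year as off treatment.
- **Analysis.** Section 9.6 compares month-24 log viral load between allocated groups by intent-to-treat, adjusted for baseline viral load and CD4 count. It provides estimation for patients who withdraw before month 24. It is silent on patients who are in follow-up but still on HAART.

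**The concern.** Taken together, these sections admit patients for whom the protocol itself, at day 0, already names a reason why the time-limited course may not end at month 12. In the treated arm such a patient may have no off-treatment viral load at month 24 or 36, yet section 9.6 puts whatever value is measured into the comparison. An on-drug value is far below a set point, and the HBV exception applies only to the arm that was given HAART. The likely error is therefore towards a benefit of TL-HAART. Adjusting for baseline viral load and CD4 does not remove on-drug suppression. The target difference is only 0.25 log10, so a few such patients could count.

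**Working it through.** **Inputs from the protocol.** Off-treatment set point 4.2 log10 with SD 0.5, target difference 0.25 log10 and alpha 0.05 (section 9.4); 90 per group (section 9.4); maximal suppression below 50 copies/mL (section 5.2), and log10(50) = 1.70.

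**Assumptions, not in the protocol.** A share f of the treated arm has HBV, is still on HAART at month 24 and sits at 1.70 log10. No control is on HAART. There is no true effect. The values f = 2%, 5% and 10% are illustrative.

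**Reproducing the plan's own figures.** n per group = 2(z₁ + z₂)² × SD² / difference².
- 80% power: 2 × (1.96 + 0.84)² × 0.25 / 0.0625 gives 63 (stated 64).
- 90% power: 2 × (1.96 + 1.28)² × 0.25 / 0.0625 gives 85 (stated 84).
- Power with 90 per group: 0.25 / (0.5 × √(2/90)) = 3.354; 3.354 − 1.96 = 1.394; power 91.8% (stated: more than 90%).

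The figures reproduce with a two-sided test.

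**Shift in the arm difference.** Shift = f × (4.2 − 1.70) = 2.5f.

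**Treated-arm SD.** √[(1 − f) × 0.25 + f(1 − f) × 2.5²].

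**Chance of a significant result with no effect** (normal approximation, unadjusted comparison, nominal 5%). SE = √[(SD² + 0.25)/90].

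| f | Patients of 90 | Shift (log10) | Treated-arm SD | Chance of significance |
|---|---|---|---|---|
| 2% | 1.8 | 0.05 | 0.61 | about 9% |
| 5% | 4.5 | 0.125 | 0.73 | about 27% |
| 10% | 9 | 0.25 | 0.89 | about 64% |

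**If the assumptions soften.** The shift depends on the difference between arms in the share on HAART. With 5% of the treated arm and 2% of controls suppressed on HAART it is (0.05 − 0.02) × 2.5 = 0.075. If only half of the assumed treated-arm share stays suppressed, each shift halves.

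**Leaving HBsAg-positive patients out of both arms, without replacement.** Power at 0.25 log10 and SD 0.5 is 91.3% (88 per arm, 2%), 90.6% (86 per arm, 5%) and 88.9% (81 per arm, 10%). Keeping 180 in the comparison means enrolling 180/(1 − f) = 184, 190 or 200.

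**The case against.** Several stronger readings are tempting, and the protocol does not support them.

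- **That only an entry exclusion can repair this.** Surface antigen is sampled before randomisation in both arms. An analysis that omits positive patients from both arms conditions on a baseline variable only, and so remains a fair randomised comparison.
- **That HBV-positive controls stay untreated.** Section 6.1.4 and note 7 of Appendix II provide for patients who start HAART for clinical or immunologic reasons. Controls on HAART at month 24 would reduce the bias.
- **That the bias is known to be large.** No prevalence is given, and nothing in the text ties recruitment of injection drug users to an HBV frequency. The 0.25 log10 row needs 10% of the treated arm suppressed on HAART. At 2% the shift is a fifth of the target.
- **That the entry criteria were meant to mirror the reasons for not stopping.** This is inference. CD4 below 350 is also the protocol's threshold for considering HAART, and 4.2.2 requires two low counts where 5.1 does not.
- **That HBsAg-positive means chronic HBV.** One screening result does not establish chronicity.

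It can also be said that broad entry is deliberate (the Schema tests a strategy in as many patients as possible) and that an analysis plan not shown here may define the population. The first point is a reason to prefer the analysis route to an exclusion. The second does not settle the matter, because section 9.6 already fixes an intent-to-treat comparison, and no section says how it accommodates the exception in 5.1.

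**Conclusion.** The inconsistency stands on the current text: chronic HBV is a named contraindication to stopping, screening can flag HBV infection before allocation, eligibility ignores it, and the month-24 comparison takes all allocated patients although the objective concerns viral load off treatment. The direction is probably in favour of TL-HAART. The size cannot be established from the protocol. The range of 0.05 to 0.25 log10 holds only if 2% to 10% of the treated arm is suppressed on HAART because of HBV and no control is on HAART, and the true figure is smaller to the extent that either condition fails. It would be wrong to infer that a false-positive result is likely. The supportable conclusion is that the plan leaves an avoidable source of bias which a test already on the schedule can remove.

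**What to change.** Reconcile sections 3.0 and 5.1, 4.2, 6.1.6, 9.6 and Appendix II for patients who are HBsAg-positive at screening, by one of two routes:

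1. Make HBsAg positivity at screening an entry exclusion in 4.2. The result must then be available before randomisation.
2. Keep these patients in the trial, but state in 9.6 that the primary set-point comparison leaves HBsAg-positive patients out of both arms, and report the all-randomised comparison as a sensitivity analysis.

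The cost is small. No new test is needed. Without replacement, power falls by about 0.5, 1.2 or 2.9 percentage points at 2%, 5% or 10%, the differences between 91.8% and the figures above. With replacement, the cost is the extra recruitment shown. The primary result would not apply to HBV co-infection, and some HBsAg-positive patients without chronic HBV would be left out as well.

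This deals with HBV only. Treated patients who stay on HAART because of a later CD4 count below 350 or pregnancy, and controls who start HAART, raise the same analysis question and remain open. No change to the treatment-stopping rule is proposed, and no view is taken on it.

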5.2 Management of inadequate viral suppression

Virologic failure will be defined as:

1. For subjects who have achieved maximal virologic suppression (HIVRNA < 50 copies/mL), a confirmed value >50 copies/mL at any time following the 6 month visit.
2. For subjects who have not achieved maximal virologic suppression (HIVRNA < 50 copies/mL) at 6 months, a confirmed 5-fold increase from nadir (e.g. a participant whose lowest HIVRNA was < 100 but rebounds to > 500).

Participants on HAART who have viral rebound (HIVRNA >50 copies/mL) will be contacted by the study staff and questioned about adherence, diet or concomitant medications in an effort to identify factors which may have led to the rise in viremia. If two successive viral load measurements are >400 copies/mL, treatment may be modified.

The revised regimen will be selected by the study physician. All investigators, project directors and study coordinators will participate in monthly team conference calls which will be moderated by [name]. All changes in antiretroviral therapy will be discussed on the monthly call.

| **Nucleoside/Nucleotide Reverse Transcriptase Inhibitors (NRTIs)** |  |
| --- | --- |
| Abacavir | 300 mg bid (or 600 mg qd if approved by the FDA during the study period) |
| Didanosine (Videx EC^®^ formulation) | 250-400 mg qd depending on body weight^(1)^ |
| Lamivudine | 150 mg bid or 300 mg qd |
| Stavudine | 30-40 mg bid depending on body weight (80-100 mg qd of Zerit XR^®^ formulation if it becomes available during study period)^(1)^ |
| Tenofovir DF | 300 mg qd |
| Emtricitabine | 200 mg qd |
| Zidovudine | 300 mg bid |
| **Non- Nucleoside Reverse Transcriptase Inhibitors (NNRTIs)** |  |
| Efavirenz | 600 mg qd |
| Nevirapine | 200 mg bid (following 2 weeks of 200 mg qd) |
| **Protease Inhibitor (PIs)** |  |
| Amprenavir | 1200 mg bid |
| Amprenavir/Ritonavir Table A: Approved Antiretroviral Agents (June 2004) | 600/100 mg bid or 1200/200 mg qd |
| Atazanavir | 400 mg qd |
| Atazanavir/Ritonavir | 300/100 mg qd |
| Indinavir/Ritonavir | 800/100 mg bid |
| Fosamprenavir | 1400 mg bid |
| Fosamprenavir/Ritonavir | 700/100 mg bid or 1400/200 mg qd |
| Lopinavir/Ritonavir | 400/100 mg bid |
| Nelfinavir | 1250 mg bid |
| Saquinavir /Ritonavir | 1000/100 mg bid or 1600-2000/100 qd |

(1): Dose adjusted based on weight or drug interactions.

### 5.3 Product Formulation and Preparation

All products will be prescribed and used in their up-to-date commercial formulations.

### 5.4 Product Supply, Distribution, and Pharmacy

5.4.1 Study Product Acquisition

All antiretroviral agents administered in the course of the study will be obtained from commercial pharmacies and dispensed according to usual good clinical practice (GCP) guidelines.

5.4.2 Study Product Accountability

Accountability of medication dispensed by commercial pharmacies will be in accordance with local regulations.

### 5.5 Concomitant Medications

5.5.1 Required Medications

There are no required concomitant medications in this study.

5.5.2 Prohibited Medications

Use of systemic cancer chemotherapy, systemic investigational agents,

immunomodulators (growth factors, systemic corticosteroids, HIV vaccines, immune

globulin, interleukins, interferons) are prohibited throughout the course of this study. In

addition, any medications that, according to the product insert(s), cannot be

coadministered with the antiretroviral agents prescribed for a given patient are

prohibited for that patient.

5.5.3 Precautionary Medications

Any medication for which, according to the product insert(s), it is advised that precautions be taken in co-administration with the antiretroviral agents prescribed for a given patient will be precautionary for that patient.

###

### 5.6 Adherence Assessment

Adherence to HAART will be assessed by the administration of the AIEDRP adherence questionnaire (Appendix IV) at each study visit while on therapy.

## 6.0 CLINICAL AND LABORATORY EVALUATIONS

All evaluations will be performed according to the Schedule of Events (Appendix II). The definitions for the Schedule of Events included in section 6.1 define the evaluations and provide timelines, and section 6.2 includes special considerations or instructions for evaluations.

6.1.1 Prestudy evaluations

Screening

Screening evaluations to determine eligibility must be completed no more than 14 days before study randomization.

Entry

Entry evaluations must occur within 14 days of the completion of all screening evaluations. In the event that results of the genotype are not available, the patient will be randomized and if necessary his/her HAART regimen will be adjusted upon receipt of the genotype. Subjects are expected to start treatment within 24 hours of randomization. (section 6.2.3).

